## 1.0 Revision History

| Version | Date finalized / updated | Summary of changes                                            | Reason for change |
|---------|--------------------------|---------------------------------------------------------------|-------------------|
| 1.0     | Dec 2, 2024              | First version                                                 | —                 |
| 1.1     | Jan 7, 2025              | Revised following in-person protocol support at KHGRAC        | —                 |
| 1.2     | Feb 12, 2025             | Revised following in-person data-management support at KHGRAC | —                 |

## 2.0 Terms and Abbreviations

| Term / Abbreviation                          | English | Definition (Japanese source)                                                                                                |
|----------------------------------------------|---------|-----------------------------------------------------------------------------------------------------------------------------|
| Dean of Faculty of Medicine                  | —       | Dean of the Faculty of Medicine, Kindai University                                                                          |
| Ethical Guidelines for Life/Medical Research | —       | Ethical Guidelines for Life Science and Medical Research Involving Human Subjects (MEXT/MHLW/METI Notification No. 1, 2021) |
| Our hospital                                 | —       | Kindai University Hospital                                                                                                  |
| Our university                               | —       | Faculty of Medicine, Kindai University                                                                                      |
| Ethics Committee                             | —       | Ethics Committee, Faculty of Medicine, Kindai University                                                                    |
| Declaration of Helsinki                      | —       | World Medical Association Declaration of Helsinki (latest revision)                                                         |
| COI Committee                                | —       | Conflict of Interest Management Committee, Faculty of Medicine, Kindai University                                           |

|           |                                                                         |                                                     |
|-----------|-------------------------------------------------------------------------|-----------------------------------------------------|
| CT        | Computed tomography                                                     | Computed tomography                                 |
| EAT-10    | Eating Assessment Tool-10                                               | Swallowing screening questionnaire (10 items)       |
| EMT       | Expiratory muscle training                                              | Expiratory muscle training                          |
| KHGRAC    | Kindai Hospital Global Research Alliance Center                         | —                                                   |
| PAS score | Penetration–Aspiration Scale score                                      | Severity scale for laryngeal penetration/aspiration |
| PPCs      | Postoperative pulmonary complications                                   | Postoperative pulmonary complications               |
| UMIN-CRT  | University Hospital Medical Information Network Clinical Trial Registry | Clinical trial registration system operated by UMIN |

### 3.0 Study Milestones / Timeline

| Date         | Milestone                                                                 |
|--------------|---------------------------------------------------------------------------|
| Dec 2024     | Draft Ver. 1.0 completed                                                  |
| Jan 2025     | Draft Ver. 1.1 completed                                                  |
| Feb 2025     | Draft Ver. 1.2 completed                                                  |
| Apr 2025     | Ethics approval; institutional authorization;
start patient enrollment |
| Sep 30, 2028 | End of patient enrollment                                                 |
| Mar 31, 2029 | End of follow-up                                                          |
| Jun 30, 2029 | End of analysis; report study completion to
Ethics Committee           |
| Mar 31, 2030 | Dissemination of results (manuscript
publication)                      |

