### **6.2 Study Population**

Patients with thoracoabdominal esophageal cancer at Kindai University Hospital who are scheduled to undergo esophagectomy with reconstruction after neoadjuvant therapy.

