#### **6.2.1 Inclusion Criteria**

- Planned esophagectomy with reconstruction at Kindai University Hospital; scheduled for neoadjuvant therapy; age  $\geq 40$  years
- First-line treatment for esophageal cancer
- No severe comorbidity of major organs (bone marrow, heart, liver, kidneys, etc.)
- Written informed consent obtained after adequate explanation
- Independent ambulation

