#### **6.2.4 Randomization and Allocation**

This study is conducted as part of routine preoperative respiratory rehabilitation under health insurance; participants will perform either sham EMT (control) or EMT (intervention) as a component of the rehabilitation program. After obtaining consent, participants will be randomly assigned using the UMIN medical research support (case registration and allocation) system, cloud version [INDICE cloud]. Allocation factors are: age (<65, ≥65), sex (male/female), and baseline PAS score category: 1–2 (no dysphagia), 3–5 (dysphagia), 6–8 (aspiration). Allocation will be performed using a non-deterministic minimization method. These factors are based on reports indicating associations of age and sex with swallowing function, and to balance baseline swallowing function between groups. The INDICE cloud randomization program will be prepared with data-management support from KHGRAC and managed strictly to prevent external disclosure. Participants and outcome assessors will be blinded to allocation.

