##### **Preoperative respiratory rehabilitation (during neoadjuvant therapy period)**

###### **Control group (Sham EMT):**

- Device instruction and load adjustment during the neoadjuvant therapy period
- Expiratory load fixed at the minimum device setting: 10 cmH2O
- 30 breaths per set; 2–3 sets/day; completion criterion: ≥5 days/week

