### 6.6.2 Study Period

Overall study period: From institutional authorization date to March 31, 2030.

Data accumulation / enrollment period: From institutional authorization date to March 31, 2029.

Analysis period: April 1, 2029 to June 30, 2029.

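### Section 3.0 counts six months of follow-up from the end of enrolment, but the last visit is counted from surgery, so late-enrolled patients cannot reach it by the stated end of follow-up

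*Protocol*

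**What the plan says.** Section 3.0 (Study Milestones / Timeline) lists "Sep 30, 2028 | End of patient enrollment" and "Mar 31, 2029 | End of follow-up". It then places both the end of analysis and the completion report to the Ethics Committee at 30 June 2029.

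Section 6.6.2 (Study Period) has "Data accumulation / enrollment period: From institutional authorization date to March 31, 2029", followed by "Analysis period: April 1, 2029 to June 30, 2029". The overall study period in that section runs to 31 March 2030.

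The order of events for a patient comes from several places:

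- Section 6.2.1: at entry the patient is "scheduled for neoadjuvant therapy; age" at least 40 years.
- Section 6.2: the patient is "scheduled to undergo esophagectomy with reconstruction after neoadjuvant therapy".
- Section 6.2.4: "After obtaining consent, participants will be randomly assigned". The assessment schedule in 6.6.1 puts consent in the column for the start of neoadjuvant therapy.
- Section 6.2.5: the training belongs to "Preoperative respiratory rehabilitation (during neoadjuvant therapy period"), so it lies between randomisation and surgery.
- Section 6.6.1: the postoperative visits are at day 10, 1 month, 3 months and 6 months, the last with a window of ± 7 days.

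**The concern.** The two dates in section 3.0 look like a plan to follow the last patient for six months. They do so only if the clock starts at enrolment, whereas the visits are timed from surgery. Between enrolment and surgery lies the whole neoadjuvant period, which is also when the training under test is given. The calendar has no room for it.

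If the dates are followed as written, the last patients reach the end of follow-up before their 6-month visit. What is then lost is the 6-month measurement of swallowing screening, tongue pressure, ultrasound of the swallowing muscles, respiratory muscle strength and appendicular muscle mass. Several of these are the secondary endpoints of section 6.5.2. The alternative is that staff collect data after the protocol says data collection has ended, and possibly after the completion report is due. In a trial of 40 patients, a handful of administratively missing 6-month visits is noticeable, and it is avoidable.

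**Working it through.** **Inputs from the protocol.** End of enrolment 30 September 2028 and end of follow-up 31 March 2029 (3.0); last visit 6 months ± 7 days after surgery (6.6.1); target 40 patients (8.1); enrolment from April 2025 (3.0).

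**Assumptions, because the protocol gives no figure.** Interval from enrolment to surgery: 0 to 20 weeks for the dates, 2 to 4 months for the patient count. Accrual: even over the enrolment period.

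**Step 1. Reproduce the stated gap.** 30 September 2028 to 31 March 2029 = 182 days. 30 September 2028 + 6 months = 30 March 2029. The stated end of follow-up is thus reproduced by counting six months from enrolment, with no interval before surgery.

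**Step 2. Count from surgery instead.** Nominal visit = enrolment date + interval to surgery + 6 months; the window is ± 7 days. For a patient enrolled on 30 September 2028:

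| Interval to surgery (assumed) | Surgery | Nominal 6-month visit | Earliest permitted date | Earliest date minus 31 Mar 2029 | Nominal date minus 31 Mar 2029 |
|---|---|---|---|---|---|
| 0 weeks | 30 Sep 2028 | 30 Mar 2029 | 23 Mar 2029 | −8 days | −1 day |
| 4 weeks | 28 Oct 2028 | 28 Apr 2029 | 21 Apr 2029 | 21 days | 28 days |
| 8 weeks | 25 Nov 2028 | 25 May 2029 | 18 May 2029 | 48 days | 55 days |
| 12 weeks | 23 Dec 2028 | 23 Jun 2029 | 16 Jun 2029 | 77 days | 84 days |
| 16 weeks | 20 Jan 2029 | 20 Jul 2029 | 13 Jul 2029 | 104 days | 111 days |
| 20 weeks | 17 Feb 2029 | 17 Aug 2029 | 10 Aug 2029 | 132 days | 139 days |

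**Step 3. Find the break point.** Surgery on 7 October 2028 gives a nominal visit on 7 April 2029, and 7 April − 7 days = 31 March 2029. This is the latest surgery date whose window still touches the stated follow-up. For the last patient it allows 7 days between enrolment and surgery, so the result does not depend on the exact length of neoadjuvant therapy.

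**Step 4. Count the patients.** April 2025 to September 2028 is 42 months, so even accrual is 40/42 = 0.95 patients per month. Those enrolled in the last 2 to 4 months are affected: 40/42 × 2 = 1.9 and 40/42 × 4 = 3.8, or about 5% to 10% of 40. If the 40th patient is enrolled earlier than the last date by at least the interval to surgery, the number is 0.

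**Step 5. Check which other visits survive.** With 2 months to surgery, the last patient has surgery about 30 November 2028 and the 3-month visit about 28 February 2029, which is inside follow-up. With 4 months, surgery is about 30 January 2029; the day-10 and 1-month visits fit, but the 3-month visit (about 30 April 2029) does not. A 3-month visit is nominally inside follow-up if surgery is by 31 December 2028, so at a 4-month interval only about the last month of enrolment is affected: 40/42 × 1 = about 1 patient.

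**The case against.** **The date in section 6.6.2 probably closes data collection, not enrolment.** It carries one combined label, coincides with the end of follow-up in 3.0, and is followed by analysis the next day. Section 3.0 holds the only date given for enrolment alone. This stands. A reader might infer from 6.6.2 that enrolment runs for 48 months, and so compute that 40/48 × (8 to 10) = 6.7 to 8.3 patients lose the 6-month visit and 40/48 × (2 to 4) = 1.7 to 3.3 have no postoperative data. Those figures rest on the less likely reading and should not be used. The wording still has to be reconciled, because as printed it names enrolment. The charitable reading also leaves the main problem in place: data collection still stops on 31 March 2029.

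**The loss is not certain.** Accrual may finish early, no section says an outstanding visit is abandoned, and section 7.2 allows amendments. This also stands, so the count must include zero. But the protocol permits enrolment to the stated date, and its calendar should support what it permits.

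**The primary analysis is not shown to suffer.** A reader might infer that these patients lose their primary outcome. The documents do not support that. Section 6.5.1 names the PAS score without a visit, 6.4.4 places the swallowing study only at the start of neoadjuvant therapy and postoperatively, and the 6.6.1 schedule has no row for it. For the same reason the loss cannot simply be set against the sample-size reserve of section 8.1 (40 × 0.95 × 0.90 = 34.2 evaluable against 32 required). That reserve concerns the primary comparison.

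**Conclusion.** The point holds as a calendar error. The 182 days in section 3.0 cover six months from enrolment, and the schedule requires six months from surgery. Any interval from enrolment to surgery above 7 days puts the last patient's whole 6-month window beyond the stated end of follow-up. With an assumed 8 to 16 weeks, the earliest permitted date is 48 to 104 days late. At 16 weeks the nominal visit (20 July 2029) also falls after the completion report.

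The size is modest: about 2 to 4 of 40 patients under even accrual and 2 to 4 months to surgery, and none if accrual ends early. What is at risk is the 6-month assessments and, at the long end of the assumed interval, the 3-month visit of about one patient. Loss of the primary PAS score is not shown. The conflict between 3.0 and 6.6.2 over the end of enrolment is real on the page but is probably a labelling fault.

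**What to change.** 1. State one end-of-enrolment date in 3.0 and 6.6.2, and relabel the 6.6.2 period ending 31 March 2029 so that it does not also read as an enrolment period.
2. Then choose one of two repairs:
   - **Move the end.** Define the end of follow-up as the last patient's surgery + 6 months + 7 days, and move the analysis and completion-report dates with it. With enrolment to 30 September 2028 and 2 to 4 months to surgery, follow-up would end between about 6 June and 6 August 2029. For example, follow-up to 30 September 2029 and analysis to 31 December 2029 would fit within the overall period to 31 March 2030.
   - **Close enrolment earlier** by the expected interval to surgery. To keep the nominal visit by 31 March 2029, enrolment would close about 5 August 2028 (8 weeks), 8 July 2028 (12 weeks) or 10 June 2028 (16 weeks).
3. State the expected enrolment-to-surgery interval on which the dates rest.

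The cost is a change of dates in two sections through the amendment route of 7.2. The first repair finishes the analysis some months later; the second shortens the enrolment window slightly.

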## 4.0 Background and Rationale

Esophagectomy with reconstruction is a highly invasive curative treatment for esophageal cancer. Surgery-related complications after esophagectomy include pulmonary complications, anastomotic leakage, anastomotic stricture, recurrent laryngeal nerve palsy, and dysphagia. In our institutional data, the postoperative pneumonia rate decreased from 25.9% (through fiscal year 2019, predominantly open thoracotomy) to 18.0% (fiscal years 2020–2023, after transitioning to minimally invasive approaches), suggesting that postoperative pulmonary complications (PPCs) are declining with less invasive surgery (unpublished data). However, postoperative dysphagia after esophagectomy has remained relatively constant at approximately 15% in our data from fiscal years 2016–2023 (unpublished data).

Prior research in esophageal cancer patients undergoing esophagectomy has reported that recurrent laryngeal nerve palsy (OR 6.6, 95% CI 1.30–33.8) and preoperative CT-measured suprahyoid/geniohyoid muscle cross-sectional area (OR 3.6, 95% CI 1.16–11.1) are significant predictors of postoperative dysphagia. In addition, preoperative tongue pressure, an index of suprahyoid and swallowing-muscle strength, has been reported as a predictor of aspiration pneumonia after esophagectomy. Furthermore, laryngeal elevation is known to significantly influence swallowing after esophagectomy, and reduced laryngeal elevation distance on postoperative videofluoroscopic swallowing studies has been associated with aspiration.

Expiratory muscle training (EMT), which applies expiratory resistance during exhalation, has been investigated as an intervention for dysphagia. Because EMT induces activity in orofacial and pharyngeal muscles (e.g., submandibular, palatal, lingual, and pharyngeal muscles), it may improve muscle strength and cross-sectional area, contribute to the coordination of bolus transport, maintain swallowing safety and efficiency, and lead to functional improvement. A meta-analysis of randomized controlled trials in stroke patients reported that EMT improved the PAS score by  $-0.81$  (95% CI  $-1.19$  to  $-0.43$ ;  $I^2=39\%$ ;  $P<0.0001$ ). EMT is believed to enhance muscular and neural adaptations relevant to swallowing recovery, with direct effects in reducing aspiration and pharyngeal residue.

## 5.0 Study Objectives

- (1) To evaluate, in a phase II single-blind randomized controlled trial, the efficacy of EMT performed during the preoperative neoadjuvant therapy period on postoperative swallowing function in patients with thoracoabdominal esophageal cancer scheduled for esophagectomy with reconstruction.
- (2) To compare the incidence of aspiration (PAS score  $\geq 6$  on postoperative videofluoroscopic swallowing study) between the two groups and estimate the effect size. The estimated effect size will be used to design a future multicenter collaborative study protocol.

Significance: Demonstrating the efficacy of preoperative EMT for preserving postoperative swallowing function in esophageal cancer patients will provide evidence for preoperative rehabilitation interventions aimed at maintaining/improving swallowing function as minimally invasive surgery advances and the surgical population ages.

## **6.0 Methods**

### **6.1 Study Design**

Prospective interventional study; single-blind randomized controlled trial (phase II).

### **6.2 Study Population**

Patients with thoracoabdominal esophageal cancer at Kindai University Hospital who are scheduled to undergo esophagectomy with reconstruction after neoadjuvant therapy.

#### **6.2.1 Inclusion Criteria**

- Planned esophagectomy with reconstruction at Kindai University Hospital; scheduled for neoadjuvant therapy; age  $\geq 40$  years
- First-line treatment for esophageal cancer
- No severe comorbidity of major organs (bone marrow, heart, liver, kidneys, etc.)
- Written informed consent obtained after adequate explanation
- Independent ambulation

#### **6.2.2 Exclusion Criteria**

- Planned two-stage esophageal reconstruction or planned total laryngectomy
- Meets contraindications for EX-1 Medic® EMT device, including: frequent asthma exacerbations; tympanic membrane perforation or similar injury; markedly elevated LV end-diastolic volume/pressure; worsening (or high likelihood) of heart failure signs/symptoms after respiratory muscle training per physician judgment; history or suspected costochondritis
- Active infection or other serious comorbidity such that EMT may increase dyspnea due to respiratory muscle fatigue, reduce consciousness due to hyperventilation, or cause syncope due to rapid hemodynamic changes associated with intrathoracic pressure shifts, as judged by the attending physician
- Difficulty enrolling due to disorientation or psychiatric illness
- High risk of pneumothorax or high physical burden from EMT due to severe emphysematous lesions or giant bullae, judged by investigators prior to surgery
- Serious conditions such as severe pneumonia, heart disease, severe liver disease, severe kidney disease; history of cardiac complications within 1 month (unstable angina, myocardial infarction, percutaneous coronary intervention, coronary artery bypass grafting) or cerebrovascular disease within 6 months; or severe emphysema/giant bullae

#### **6.2.3 Study Devices / Equipment**

- Expiratory muscle training: EX-1 Medic® (Entry Japan) (Figure 1)
- Respiratory muscle strength measurement: IOP-01 (Kohata Instrument Manufacturing)
- Exercise capacity: Aeromonitor AE-310S (Minato Medical Science Co., Ltd.)
- Ultrasound for suprahyoid muscles, sternocleidomastoid, and diaphragm thickness: Xario200 (Toshiba)

- Appendicular skeletal muscle mass: seca mBCA 525 (seca)

Note: Use of hospital-managed medical equipment will be approved by the hospital director via the appropriate application process.

#### **6.2.4 Randomization and Allocation**

This study is conducted as part of routine preoperative respiratory rehabilitation under health insurance; participants will perform either sham EMT (control) or EMT (intervention) as a component of the rehabilitation program. After obtaining consent, participants will be randomly assigned using the UMIN medical research support (case registration and allocation) system, cloud version [INDICE cloud]. Allocation factors are: age (<65, ≥65), sex (male/female), and baseline PAS score category: 1–2 (no dysphagia), 3–5 (dysphagia), 6–8 (aspiration). Allocation will be performed using a non-deterministic minimization method. These factors are based on reports indicating associations of age and sex with swallowing function, and to balance baseline swallowing function between groups. The INDICE cloud randomization program will be prepared with data-management support from KHGRAC and managed strictly to prevent external disclosure. Participants and outcome assessors will be blinded to allocation.

#### **6.2.5 Interventions**

Preoperative and postoperative respiratory rehabilitation programs

##### **Preoperative respiratory rehabilitation (during neoadjuvant therapy period)**

###### **Control group (Sham EMT):**

- Device instruction and load adjustment during the neoadjuvant therapy period
- Expiratory load fixed at the minimum device setting: 10 cmH2O
- 30 breaths per set; 2–3 sets/day; completion criterion: ≥5 days/week

###### **Intervention group (EMT):**

- Device instruction and load adjustment during the neoadjuvant therapy period
- Load starts at 50% of maximal expiratory pressure and is progressively increased up to 75%
- 30 breaths per set; 2–3 sets/day; completion criterion: ≥5 days/week

Both groups will use a training log to record daily sessions and repetitions.

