### **6.4 Data to be Collected**

The following information will be obtained from medical records:

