## 6.6 Schedule

Preoperative rehabilitation involves instruction, setting, and load adjustment of sham EMT (control) or EMT (intervention). Both groups receive breathing and cough instruction on the day before surgery. Postoperative rehabilitation follows the standard program without EMT; postoperative rehabilitation is routine care as previously practiced, whereas preoperative rehabilitation is performed for this study.

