#### 8.3.2 Adverse Events

Definitions:

Serious: falls/fractures, cardiopulmonary arrest, death.

Non-serious: hypotension, unsteadiness, dizziness, malaise.

Known: dyspnea, anxiety, palpitations, lower-limb fatigue.

Causality: Adverse events occurring during study procedures (assessment/measurement) are considered related.

Follow-up items when an adverse event occurs: symptoms/findings, onset date, outcome (A=recovered; B=improved; C=unchanged; D=recovered with sequelae; E=death), and outcome date.

Reporting: In the event of a serious or unexpected adverse event, the Principal Investigator will report to the Dean in accordance with institutional regulations. If an adverse event meets criteria for urgent reporting, sub-investigators will immediately notify the Principal Investigator.

Depending on frequency and severity, enrollment may be suspended or the trial interrupted/terminated at the discretion of the study leadership.

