### **10.4 Participant Burden, Risks, and Benefits**

The only assessment performed solely for this study is ultrasound measurement of laryngeal elevation distance and suprahyoid muscle cross-sectional area. Other interventions, examinations, and assessments performed during hospitalization (pre/postoperative) are within routine insured medical care and do not incur costs beyond usual patient co-payments. Ultrasound assessments will be conducted with the hospital director's approval for use of hospital-managed equipment, and no costs will be charged to participants.

The EMT device (EX-1 Medic®) will be purchased using research funds of [name] and provided to participants. Consumable and equipment-related costs for assessments (see the separate cost calculation document) will be covered by allocated research funds of [name]. Potential risks include adverse events during assessments; because assessments are conducted during routine clinical hours, physician support from the Department of Rehabilitation Medicine will be available if needed.

Participants will receive the EMT device as a gift; otherwise, there are no direct individual

benefits. However, study findings may contribute to future improvements in care for patients with esophageal cancer.

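### The causality rule and the risk text cover assessments but not EMT or sham training, and the training log is not described as capturing symptoms

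*Protocol*

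**What the plan says.** **Exposure.** Section 6.2.5 gives both arms the same schedule: "30 breaths per set; 2–3 sets/day; completion criterion: ≥5 days/week". The sham load is fixed at 10 cmH2O. The EMT load starts at 50% of maximal expiratory pressure and rises to 75%. Device instruction and load adjustment are planned in both arms, but their number and timing are not stated. Section 6.6 says that postoperative rehabilitation is routine, "whereas preoperative rehabilitation is performed for this study".

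**Recognised harms.** Section 6.2.2 excludes patients with active infection or serious comorbidity in whom EMT might worsen breathlessness, impair consciousness through hyperventilation, or provoke fainting. It also excludes those at high risk of pneumothorax.

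**Recording.** On the training record, section 6.2.5 says: "Both groups will use a training log to record daily sessions and repetitions". Section 6.4 opens its data list with "The following information will be obtained from medical records" and names no adverse-event item.

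**Attribution and risk.** Section 8.3.2 states: "Causality: Adverse events occurring during study procedures (assessment/measurement) are considered related". Section 10.4 states: "Potential risks include adverse events during assessments", and links physician support to the hours in which assessments take place.

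**Follow-up and action.** Section 8.3.2 also provides "Follow-up items when an adverse event occurs: symptoms/findings, onset date, outcome" and outcome date. It requires serious or unexpected events to be reported, and adds: "Depending on frequency and severity, enrollment may be suspended or the trial interrupted/terminated at the discretion of the study leadership".

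**The concern.** The safety text is aimed at the measurements, while the intervention under test is the training. Two things follow.

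First, if a patient becomes dizzy during a lung-pressure measurement, the rule makes the event related. If the same patient becomes dizzy during a training set, no rule applies, and attribution is left to whoever happens to record the event.

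Second, section 8.3.2 starts to operate once an event has been noticed. Nothing in the protocol describes a step by which mild symptoms during unsupervised training would be noticed. The daily record is described in terms of sessions and repetitions, and no symptom review is attached to the load-adjustment contacts.

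What is at stake is the quality of the tolerability data from a phase II trial meant to inform a multicentre study (section 5.0). A statistical analysis plan can decide how to summarise events. It cannot recover symptoms that nobody recorded.

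**Working it through.** There is no stated figure to reproduce on this point. The check sets the provisions side by side.

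**Step 1: does the attribution rule reach a training session?** The rule in 8.3.2 covers study procedures and explains that term in brackets as assessment and measurement. Training is neither. Section 6.6 separately says that the preoperative programme is done for the study, so training is a study activity that the bracket leaves out. Section 6.2.4 describes the programme as part of insured routine rehabilitation, and section 10.4 describes inpatient interventions in the same way. Neither statement supplies an attribution rule for a training event. Result: the rule is silent on training.

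**Step 2: does the risk text reach it?** Section 10.4 names events during assessments and the medical cover available at those times. It does not mention training. Section 6.2.2 attributes breathlessness, impaired consciousness, fainting and pneumothorax risk to EMT itself, at least in susceptible patients. Result: the protocol recognises training harms in one place and omits them where risks are described.

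**Step 3: which events lack a route to being found?**

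| Type of event during training | Provision | Gap |
|---|---|---|
| Serious | Reported under 8.3.2 | Attribution only |
| Unexpected (plausibly fainting, which is on none of the 8.3.2 lists) | Reported under 8.3.2 | Attribution only |
| Listed as non-serious or known (dizziness or dyspnea, for example), and noticed | Follow-up items in 8.3.2 apply | Attribution only |
| Listed as non-serious or known, not volunteered | No described step asks about it | Ascertainment and attribution |

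The ascertainment gap is confined to the last row. The attribution gap applies to every row.

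**Step 4: other places where collection might be specified.** The data list in 6.4 has no adverse-event item, although it draws on the medical record and includes clinical outcomes. The schedule in 6.6.1 has no adverse-event row, but it also has no row for the videofluoroscopic study that gives the primary endpoint, so its silence is weak evidence. Section 11.4 plans no monitoring or audit, so no later check would bring missed symptoms to light.

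**Step 5: scale of the exposure.** At five days a week the stated dose is 2 × 5 = 10 to 3 × 5 = 15 sets, or 10 × 30 = 300 to 15 × 30 = 450 breaths per patient per week. This describes how much activity lies outside the attribution rule. It does not measure lost events, and the protocol gives no rate from which to derive them.

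**The case against.** The strongest objection is that adverse events are already handled. The follow-up items in 8.3.2 apply to any event, whatever its seriousness and wherever it occurs, and serious or unexpected events are reported. How symptoms are asked about may be set out in log templates or case report forms that are not shown. The sentence about the log says what it is used for and does not say that it holds nothing else. This stands in part. The ascertainment point is therefore a likelihood, resting on how the log is described, and not a demonstrated absence. It does not answer the causality and risk wording, which is fixed in the protocol and leaves out the intervention.

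A second objection concerns the remedy. EMT load is progressed and sham load is not, so contacts may be more frequent in the EMT arm. Review by therapists who know the load could then produce more recorded events in that arm. This is a fair caution. It is why the symptom line should be completed by the blinded participant and be identical in both arms.

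A reader might also infer stronger conclusions that the documents do not support:

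- **That the rule classes training events as unrelated.** It only deems assessment-time events related, and says nothing about the others.
- **That event frequency by arm could not be judged.** Frequency by arm needs event counts and allocation, not attribution. The suspension clause refers to frequency and severity, not to relatedness. Under-ascertainment may make the counts incomplete, but that is a weaker statement.
- **That the exclusion of nerve-palsy patients in section 8.2 damages the safety results.** The protocol describes no safety analysis to which that exclusion would apply, and a safety population is normally defined in a statistical analysis plan.

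**Conclusion.** The point holds as a gap in attribution and a probable weakness in ascertainment. The causality rule and the risk text omit the activity that the trial is testing, and this is plain from the text. That non-serious events during self-logged sessions will be under-recorded is an inference. It assumes that the log contains what section 6.2.5 describes and that no other document adds a symptom enquiry.

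The size cannot be put in numbers, because no event rate, capture rate or length of neoadjuvant therapy is given. The primary comparison of PAS scores is not affected. The change is still worth making, because it is cheap and symptoms not recorded at the time cannot be recovered by a later analysis.

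**What to change.** 1. **Section 8.3.2:** extend the bracket in the causality rule so that study procedures include EMT and sham training sessions as well as assessment and measurement.
2. **Section 10.4:** name the risks of training, consistent with those already recognised in section 6.2.2.
3. **Section 6.2.5:** add a symptom line to the existing training log, completed by the participant and worded identically in both arms. Unblinded therapy staff, not the blinded assessors, review it at existing contacts and at the preoperative visit. Events are recorded with the follow-up items already listed in 8.3.2.

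**Cost.** These are three short text changes and one line on an existing form, handled by an amendment under section 7.2 where required. No new test or visit is needed, since review uses contacts already planned. Participants record slightly more, and therapy staff spend some time on review and data entry. Symptoms of neoadjuvant therapy will also be captured. They arise in both arms, so the sham arm gives the comparison. The identical participant-completed line limits, but does not remove, bias from any difference in contact frequency.
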